## Abstract

**Background:**

Around a quarter of the world's neonatal and maternal deaths occur in India. Morbidity and mortality are highest in rural areas and among the poorest wealth quintiles. Few interventions to improve maternal and newborn health outcomes with government-mandated community health workers have been rigorously evaluated at scale in this setting.

The study aims to assess the impact of a community mobilisation intervention with women's groups facilitated by ASHAs to improve maternal and newborn health outcomes among rural tribal communities of Jharkhand and Orissa.

**Methods/design:**

The study is a cluster-randomised controlled trial and will be implemented in five districts, three in Jharkhand and two in Orissa. The unit of randomisation is a rural cluster of approximately 5000 population. We identified villages within rural, tribal areas of five districts, approached them for participation in the study and enrolled them into 30 clusters, with approximately 10 ASHAs per cluster. Within each district, 6 clusters were randomly allocated to receive the community intervention or to the control group, resulting in 15 intervention and 15 control clusters. Randomisation was carried out in the presence of local stakeholders who selected the cluster numbers and allocated them to intervention or control using a pre-generated random number sequence. The intervention is a participatory learning and action cycle where ASHAs support community women's groups through a four-phase process in which they identify and prioritise local maternal and newborn health problems, implement strategies to address these and evaluate the result. The cycle is designed to fit with the ASHAs' mandate to mobilise communities for health and to complement their other tasks, including increasing institutional delivery rates and providing home visits to mothers and newborns. The trial's primary endpoint is neonatal mortality during 24 months of intervention. Additional endpoints include home care practices and health care-seeking in the antenatal, delivery and postnatal period. The impact of the intervention will be measured through a prospective surveillance system implemented by the project team, through which mothers will be interviewed around six weeks after delivery. Cost data and qualitative data are collected for cost-effectiveness and process evaluations.

**Study registration:**

ISRCTN: ISRCTN31567106

## Background and rationale

### Millennium development goals 4 and 5

Little time is left to achieve Millennium Development Goals (MDGs) 4 and 5 for maternal and child survival. Only 19 of 68 priority countries are on track to achieve MDG4, which calls for a two-thirds reduction in under-five mortality rates from 1990 levels [1]. Because neonatal deaths account for 41% of under-5 deaths, achieving MDG 4 requires scaling up strategies to reduce neonatal mortality [2]. Effective interventions have long been identified, and key questions now concern the best ways to increase their coverage in an equitable manner, particularly in countries and communities with high mortality rates [3-5].

### Maternal and child survival in India

Around a quarter of the world's neonatal and maternal deaths occur in India [6]. The current neonatal mortality rate (NMR) is estimated at 34.3 per 1000 live births [7] and the maternal mortality ratio at 254 per 100 000 live births [8]. The child mortality rate declined from 33.5 (24.1-45.4) deaths per 1000 live births in 1990 to 13.6 (9.0-19.7) in 2010, and the maternal mortality ratio from 523 (310-835) to 254 (154-395) between 1990 and 2008 [7,8]. To meet MDG4 however, an accelerated reduction in neonatal mortality is required as neonatal deaths account for 55% of under-five deaths [1]. Neonatal mortality rates vary widely between states, ranging from 11 in Kerala to 48 in Uttar Pradesh [9]. They also vary within states and between social groups: the NMR in rural areas is about one and a half times that of urban areas, and rates among the poorest wealth quintile are more than double those among the richest [10]. Socio-economically disadvantaged communities such as indigenous or *adivasi *groups (defined in India's demographic surveys as Scheduled Tribes) have particularly high mortality rates: *adivasi *children have a 25% increased risk of dying before the age of five compared to non-adivasi children [11].

### Current maternal and child health government programmes in India

The Government of India implements three large intersecting programmes to improve women and children's health. The first is the Reproductive and Child Health II (2005-10) programme, which includes the Integrated Management of Newborn and Childhood Illnesses (IMNCI) at community and facility-levels, promotion of skilled care at birth, Essential Newborn Care training for professionals, and health service strengthening. The second is the Integrated Child Development Services (ICDS) programme, which provides a range of nutrition interventions for women and children. The third is India's flagship National Rural Health Mission programme (2005-2012), including the *Janani Suraksha Yojana *(JSY) maternity incentive scheme under which all pregnant women living below the poverty line receive money to deliver in a health facility and receive postnatal check-ups [12]. The NRHM also finances an estimated 820,000 community health volunteers called Accredited Social Health Activists (ASHAs) in priority states. ASHAs are mandated to disseminate health information, counsel women on issues of reproductive and child health and provide essential supplies and drugs (e.g Oral Rehydration Salts and antimalarials). The ASHA programme provides an important platform for scaling up effective community-based interventions for maternal and newborn survival [13].

### Community-based interventions to improve newborn survival

Several community-based interventions have demonstrated substantial effects on neonatal mortality [14,15]. In the home-based newborn care model developed by SEARCH Gadchiroli [16] a trained community health worker identified pregnant women, conducted group health education, carried out two antenatal and 8-12 postnatal home visits, attended deliveries, gave infants a vitamin K injection, identified and managed high risk infants who had signs of sepsis by providing injectable antibiotics in the home and encouraged appropriate referral. This intervention led to a 70% reduction in neonatal mortality over 10 years of incremental implementation, was replicated with seven NGOs (Ankur study) covering around 80 000 population. Elements from home-based newborn care and home visits have been incorporated into ASHAs' training. Following this and other studies, WHO and UNICEF endorsed home visits with components of home-based newborn care as a strategy to improve newborn survival in low-resource settings [17,18]. There is now a need for operational research to examine the feasibility of scaling up this strategy, with equity as a prime concern [19].

Other models emphasise the importance of community mobilisation and participation to improve maternal and newborn health, either with or without a concurrent programme of home-based newborn care. These interventions are premised on the notion that many maternal and newborn deaths can be avoided through better understanding of health problems, changes in antenatal and newborn care practices, and improvements in community perceptions of, and demand for, health services. Several community mobilisation interventions have used a participatory approach, building on the idea that if mothers and other community members take part in decision-making and bring local knowledge, experiences and problems to the fore, they are more likely to own and sustain solutions to improve their communities' health [20]. The Shivgarh trial in Uttar Pradesh successfully tested a combined approach of home visits with social mobilisation through community change agents, leading to a 54% (RR: 0.46, 95%CI: 0.35-0.60) reduction in neonatal mortality over 15 months [21]. The Makwanpur and Ekjut trials showed reductions of 30% (OR: 0.70, 95% CI 0.53-0.94) and 45% (OR: 0.55, 95%CI: 0.46-0.66) in neonatal mortality through community mobilisation with women's groups [22,23], but it remains unclear whether this impact could be maintained if implemented at scale using existing community health workers or volunteers as women's group facilitators.

In India, the NRHM has called for both an expansion of ASHAs' training in home-based newborn care and for "constituting community-based women empowerment groups [...] with the aim to ensure that the female functionaries - ASHAs, Anganwadi workers and Auxiliary Nurse Midwives--become accountable to and work with these groups to help them realise their well-being and rights." [23] Community mobilisation for health is part of the mandate of ASHAs, but specific strategies for community mobilisation led by these workers have yet to be tested [24].

### Justification for this study

Although several intervention models have shown impacts on neonatal survival in India, we do not know whether any of these can bring improvements when delivered through government-linked community health workers such as ASHAs, nor what the barriers and facilitators to scale up might be. This trial aims to test whether a proven participatory community intervention with women's groups can improve maternal and newborn health when implemented with ASHAs, examine its interaction with home visits for maternal and newborn care, and identify the processes through which the intervention can be successfully delivered and scaled-up.

Although the women's group intervention has already been tested in three trials, we decided to adopt a cluster-randomised controlled design to evaluate its impact with ASHAs for two reasons. First, the community mobilisation intervention has not been tested when delivered by community health workers (CHWs); other programmes combining community mobilisation with essential newborn care and delivered by CHWs were not evaluated with baseline data or a control group [25]. Second, several NRHM interventions (including home visits and JSY) are being implemented in the study areas and only an RCT would allow us to robustly quantify the contribution of community mobilisation to any mortality reduction in this context.

In addition, the study is needed to address key implementation research questions and identify strategies for scaling up. Taking community health worker programmes to scale raises questions about adequate levels of remuneration, training, supervision and motivation. Providing recommendations to address these is critical: in a 2007 study, only 3-12% of children born at home in 5 south Asian and sub-Saharan African countries received a visit from a trained health worker within 3 days of birth [26]. Implementation research is necessary in order to understand how best to implement the intervention with ASHAs and whether community mobilisation will supplement or impede their existing activities.

## Design and methods

### Study design

The study is a cluster-randomised controlled trial. Cluster randomisation was preferred over individual randomization as the intervention is a community mobilisation programme delivered at a village-level and with the potential to influence health outcomes both within and between households. An implementation research component is carried out through the trial's process evaluation.

### Aim

To assess the impact and scalability of a community mobilisation intervention with women's groups facilitated by ASHAs to improve maternal and newborn health outcomes among rural tribal communities of Jharkhand and Orissa

### Objectives

1. To test the impact of a community mobilisation intervention with women's groups led by ASHAs on:

(a) Birth outcomes, including neonatal mortality and stillbirths

(b) Care practices and health care-seeking behaviour for mothers and newborns

2. To examine the contribution of community mobilisation with women's groups to maternal and newborn health outcomes in the context of other government programmes

3. To document the context, delivery and costs of the intervention in order to identify lessons for scale-up

### Primary research question

What is the effect of a community mobilisation intervention led by ASHAs on neonatal and perinatal mortality rates?

### Secondary research questions

What is the effect of the intervention on home care practices and health-care seeking behaviour?

What are the factors to consider in scaling up of this intervention, if successful?

### Trial endpoints

The trial's primary endpoint is the neonatal mortality rate over 24 months. Because we expect a short lag period for this intervention to take effect as groups take some time to discuss the causes of maternal and newborn health problems before implementing strategies, we will include data for the last 24 months of the study (1^st ^January 2011 - 31^st ^December 2012) in the final analysis for the primary endpoint, thereby allowing for a four month lag-period. Additional endpoints for the trial include home care practices and health-care seeking behaviour for mothers and newborns and ASHAs' activities related to home visits. The trial endpoints are listed in Table 1.

**Table 1 T1:** Trial outcomes and indicators

Mortality	
Neonatal mortality rate	Number of Neonatal deaths per 1000 livebirths

Stillbirth rate	Number of Stillbirths per 1000 births

Early neonatal mortality rate	Number of early neonatal deaths (0-6 days) per 1000 livebirths

Late neonatal mortality rate	Number of late neonatal deaths (7-28 days) per 1000 livebirths

Maternal mortality ratio	Number of maternal deaths per 100 000 livebirths

Pregnancy-related mortality ratio	Number of pregnancy-related deaths per 100 000 livebirths

Perinatal mortality rate	Number of perinatal deaths per 1000 births

**Care-seeking practices**	

4+ ANC visits	% of births for which mothers received 3+ ANC visits from a skilled provider (doctor, ANM, or other nurse)

Care-seeking for a problem in pregnancy	% of births for which mother had a problem in pregnancy and sought care from a qualified provider

Institutional delivery	% of births that took place at health facility (public or private)

Birth preparedness	% of births for which mothers who made a plan for the delivery

Skilled Birth Attendance	% of home births for which mothers delivered with a skilled birth attendant (doctor, ANM, or other nurse)

Care-seeking for delivery complications	% of births in which complications were identified for which mother sought skilled care

Maternal postnatal visit (qualified provider)	% of births for which mother received at least one postnatal check-up from skilled provider (doctor, ANM or other nurse)

Infant postnatal visits (qualified provider)	% of births for which child received at least one postnatal check-up from skilled provider (doctor, ANM, other nurse or ASHA)

Care-seeking for infant illness	% of births for which mothers sought care from qualified provider if infant had either fever, diarrhoea or cough in first 6 weeks

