### Setting

The study takes place in two districts of Orissa and three districts of Jharkhand, two states of eastern India. The five districts are largely rural and have a high proportion of *adivasi *people. The main tribal groups in the trial area are the Ho, Munda, Oraon, Santhal, Binjhiya, Paharia, Bhumij, Bhatudi, Bhuyian, Gond, Mankidia and Kondh. In previously published research carried out in other rural tribal areas of these states, [22] we found a neonatal mortality rate of 58 per 1000 livebirths and a maternal mortality ratio of 510 per 100 000 livebirths. Around 35% of mothers had three or more antenatal check-ups and only 17% delivered in a health facility. In December 2010, the recruitment of ASHAs had been completed in Jharkhand and Orissa but their training in home-based newborn care had not begun. JSY was operating in both states but had higher coverage in Orissa [13]. The trial is being implemented by Ekjut, an NGO that has been working in Jharkhand and Orissa since 2003, in collaboration with the Centre for International Health and Development at University College London (UK).

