##### Sub-analyses

We will compare the proportion of women who received postnatal home visits by an ASHA and the proportion of women who delivered in institutions among areas with and without ASHA-led mobilisation.

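### Skilled birth attendance is measured among home births only, so its between-arm comparison is not a randomised one if place of delivery shifts

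*Protocol article*

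**What the plan says.** In the care-seeking block of Table 1, skilled birth attendance is the percentage "of home births for which mothers delivered with a skilled birth attendant (doctor, ANM, or other nurse". The same block lists institutional delivery as a separate outcome with all births as its denominator: the percentage "of births that took place at health facility (public or private". No row gives skilled attendance over all births.

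Three other places bear on whether place of delivery can differ between arms. Objective 1(b) sets out to test the effect on "Care practices and health care-seeking behaviour for mothers and newborns". The Sub-analyses section compares "the proportion of women who delivered in institutions among areas with and without ASHA-led mobilisation". The abstract says that the cycle should "complement their other tasks, including increasing institutional delivery rates".

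The row on care-seeking for delivery complications also has a restricted denominator: the percentage "of births in which complications were identified for which mother sought skilled care". By contrast, the row on problems in pregnancy is worded as a joint event over births: the mother had a problem and sought qualified care.

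**The concern.** Randomisation makes the arms comparable for all births in the clusters. It does not do so for home births alone once the intervention affects who delivers at home. The home births left in each arm are then selected differently, and a difference in the indicator mixes two things: a change in attendance at home, and a change in who is still at home. The analysis section describes intention-to-treat analyses, and a comparison within this subgroup does not have that property.

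The indicator is also blind to one route to success. A woman who would have delivered at home unattended and goes to a facility instead adds nothing to its numerator and leaves its denominator. If she would have had a skilled attendant at home, her move lowers the numerator, although she still has skilled care. A programme that works through facility delivery could therefore show no change, or a decline, in a row headed skilled birth attendance.

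The complications row raises a related question. Its denominator depends on a complication being recognised, and groups that discuss maternal and newborn problems and prepare for emergencies may change recognition.

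**Working it through.** The protocol gives no rate of skilled attendance at home births and no expected shift in place of delivery, so there is no stated figure to reproduce on this point. The power statement concerns neonatal mortality and does not use this indicator.

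**Inputs**
- h, share of births in a facility without the intervention: 17%. The Setting section says "only 17% delivered in a health facility" and gives this for earlier research in other rural tribal areas of the two states, so it is not a control-arm figure for this trial.
- s, skilled attendance among home births: 12%, assumed.
- d, share of all births that move from home to a facility: 10 points, assumed.
- f, share of those movers who would have had a skilled attendant at home: varied over 40%, 20%, 12% and 5%, assumed.
- Facility births count as skilled-attended, and attendance among women who stay at home is otherwise unchanged.

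**Formulas**
- Home-only indicator after the shift: [(1 − h)s − d·f] / (1 − h − d).
- Change in the home-only indicator: d(s − f) / (1 − h − d). It falls if f > s, is flat if f = s and rises if f < s.
- All-births attendance before the shift: h + (1 − h)s. Change: d(1 − f), which is positive whenever f < 1.

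**Before the shift**
- Skilled home births: 0.83 × 0.12 = 0.0996 of all births.
- Home-only: 0.0996 / 0.83 = 12.0%.
- All births: 0.17 + 0.0996 = 0.2696, or 27.0%.

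**After the shift** (facility share 0.27, home share 0.73)

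| f | Skilled home births | Home-only | All births |
|---|---|---|---|
| 40% | 0.0996 − 0.040 = 0.0596 | 0.0596 / 0.73 = 8.2% | 0.27 + 0.0596 = 33.0% |
| 20% | 0.0996 − 0.020 = 0.0796 | 0.0796 / 0.73 = 10.9% | 0.27 + 0.0796 = 35.0% |
| 12% | 0.0996 − 0.012 = 0.0876 | 0.0876 / 0.73 = 12.0% | 0.27 + 0.0876 = 35.8% |
| 5% | 0.0996 − 0.005 = 0.0946 | 0.0946 / 0.73 = 13.0% | 0.27 + 0.0946 = 36.5% |

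The all-births figure rises by 6.0 to 9.5 points throughout. The home-only figure moves by −3.8 to +1.0 points, although by construction nothing changed for women who stayed at home. All of that movement is selection.

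**Complications.** Let c be the share of births with a complication identified and q the share of those for which skilled care was sought. Suppose better recognition adds Δ births, of which a share g seeks skilled care. The listed indicator becomes (cq + Δg) / (c + Δ), which rises or falls according to whether g exceeds q. The joint proportion over all births becomes cq + Δg, which rises with recognition whenever g > 0. Neither is interpretable without c. The documents give no value for c, q, Δ or g, so no size can be attached.

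**The case against.** The strongest reply is that Table 1 already holds both pieces. Institutional delivery over all births is in the same block, the Sub-analyses section compares it between arms, and the attendance row says openly that it covers home births. A reader could combine the two rows as h + (1 − h)s and would see a move to facilities alongside any fall at home. This stands in part and limits the harm. But the combination is not planned, and two separate percentages do not yield a cluster-adjusted comparison of overall attendance.

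Second, the shift is not a stated expectation. A reader might infer from the abstract that the intervention is expected to raise facility delivery. The words "including increasing institutional delivery rates and providing home visits to mothers and newborns" describe tasks that ASHAs already have. The Setting section says that the maternity incentive scheme operates in both states, and the justification section leaves open whether mobilisation will help or hinder the ASHAs' existing work. The documents support only that place of delivery may change.

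Third, a fall in the indicator is not inevitable. It depends on f exceeding s, and no part of the protocol says that women inclined to use a skilled attendant move first. At f = 12% the indicator is flat and at 5% it rises. This stands, and for that reason the range is shown. The case at 40% is a strong one, since it moves 0.040 / 0.0996, about 40%, of all skilled home births into facilities.

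Fourth, a reader might infer that extra complications recognised in intervention clusters would be milder ones. The protocol does not say so. Recognition may change, and nothing more can be said.

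**Conclusion.** The point holds as a defect in the definition of one secondary indicator, with a related but less certain point on the complications row. If place of delivery differs between arms, the home-only comparison is not randomised and omits gains made through facility delivery. It moves against overall attendance only if women who shift were likelier than other home-birthing women to have had a skilled attendant. Under the illustrated inputs the home-only figure ends anywhere from 8.2% to 13.0%, from a start of 12.0%, while overall attendance rises in every case. The 12%, the 10 points and all values of f are assumptions, and the 17% comes from other areas.

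Two stronger conclusions are not supported. A reader might infer that the stopping decision is at risk. The Stopping rules section refers to care-seeking indicators only collectively, together with implementation quality, and names neither row, so the link is indirect. A reader might also extend the criticism to the clean delivery practices. Those items are explicitly limited to home births because they concern how a home delivery is conducted, and they can stay as they are. The primary endpoint and its power are unaffected.

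**What to change.** In Table 1, define skilled birth attendance over all births: facility births plus home births attended by a doctor, ANM or other nurse, divided by all births. Report the home-birth figure beside it as descriptive.

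For delivery complications, keep the existing row and add two figures over all births: the proportion with a complication identified, and the joint proportion with a complication identified and skilled care sought. The joint form follows the wording that Table 1 already uses for problems in pregnancy. Since it also rises with recognition, state that it is to be read with the proportion identifying a complication. Leave the clean delivery items unchanged.

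The attendance change costs one more derived row, built from place of birth and attendant at home births, both of which Table 1 already requires. The complications figures likewise use the two items that the existing row needs. The drawback is that facility births are counted as skilled-attended, which should be stated in the table.
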